### Secondary outcomes

Time to symptomatic remission

Symptomatic remission is defined as a score of 3 or less on each of the PANSS items P1, P2, P3, N1, N4, N6, G5 and G9, regardless of whether or not this response is sustained for 6 months (i.e. response, but does not reach the duration criterion for recovery).2.Relapse

Relapse outcome is defined as the proportion of participants who relapse at least once during the 12-month follow-up period. Relapse is defined as a score of 4 or more on at least one of the PANSS items P1, P2, P3, N1, N4, N6, G5 or G9 after initial symptomatic remission occurred during the 12-month follow-up period.3.Number of adverse events (AEs) over the 12-month follow-up period

The total number of AEs, total number of serious adverse events (SAEs) and total number of AEs with grade III or IV as reported in the AE CRF over the 12-month follow-up period will be presented by randomised group.4.Number of serious infections

The total number of reported serious infections and the number of serious infections per participant over the 12-month follow-up period will be reported for each randomised group.5.Proportion of patients reaching 20%, 30% and 40% reduction in PANSS total score over the 12-month follow-up period.

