### Sample size

To estimate the control rate for the primary outcome efficacy measure, we have re-analysed the raw data of the National EDEN study [27]. This study consisted of 1000 patients with psychosis (antibody associations not known); 19% of those, who were symptomatic at entry, experienced sustained remission as per the Andreasen et al. criteria [21] on standard antipsychotic therapy at 1 year. The 50% remission rate on immunotherapy that we have selected is a conservative estimate; in anti-NMDAR encephalopathy, remission may be as high as 85% at 1 year following IVIG and rituximab [7]. We agreed on 50% as a clinically meaningful and important remission rate that from a patient perspective would make participation in the trial acceptable. The Trial Steering Committee (TSC) and statistician will analyse recruitment and dropout rates at months 12 and 24 of the trial, and consider altering the recruitment strategy. We have chosen a sample size to target a time-to-remission hazard ratio of 0.322 with a one-sided type I error rate of 5% and a power of 80%, standard for a stage II clinical trial. This target hazard ratio comes from assuming a 1-year remission probability of 0.2 in the control arm and 0.5 in the experimental arm and assuming the time-to-remission distribution is exponential with proportional hazards. With all participants followed up for 1 year, a sample size of 56 participants equally randomised between the control and experimental arms is required. The sample size was calculated using NCSS PASS v14. We intend to recruit about 80 participants, allowing dropout of 12 participants per arm. This level of dropout is a cautious estimate because, although a high dropout is often seen in drug trials in psychosis, we are not requiring continued compliance with medication regimes after the infusions of IVIG and rituximab.

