### Statistical analysis methods

The final analysis will use a Cox proportional hazards model with fixed effects for minimisation covariates. The primary analysis will be per protocol rather than intention to treat, although both will be done. Secondary and exploratory outcomes will be analysed with Cox models (time to any remission), logistic regression models (relapse rate, proportion of participants with serious adverse events) and Poisson models (number of adverse events). The per-protocol population is defined as all participants who have received all protocol-defined IMPs, and have no major protocol violation as defined prior to analysis. A full detailed analysis plan will be prepared by a statistician who is independent from the study.

Data on trial progress such as recruitment and participant dropout at months 12, 24 and 36 of the trial (after activation of the first site) and quality of data will be reported to both the Trial Steering Committee and the Data Monitoring Committee (DMC). The Trial Steering Committee will consider opening additional sites and/or modifying eligibility criteria if recruitment rates are below those expected. There will be no interim analyses of efficacy.

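### The Poisson model named for adverse-event counts can give intervals that are too narrow, because nothing is said about overdispersion or unequal follow-up

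*Protocol article*

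**What the plan says.** Safety is the trial's one secondary objective (Trial objectives). Item 3 of Secondary outcomes is "Number of adverse events (AEs) over the 12-month follow-up period". Its components are "The total number of AEs, total number of serious adverse events (SAEs) and total number of AEs with grade III or IV", to be shown for each randomised group.

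Statistical analysis methods gives a model family for each kind of secondary outcome: Cox for time to any remission, "logistic regression models (relapse rate, proportion of participants with serious adverse events"), and "Poisson models (number of adverse events"). It does not say whether the Poisson standard error is model-based, scaled or robust, and it mentions no offset. It then announces further detail: "A full detailed analysis plan will be prepared by a statistician who is independent from the study".

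Two other sections bear on time at risk. Sample size states: "We intend to recruit about 80 participants, allowing dropout of 12 participants per arm". Withdrawal keeps participants who stop treatment in follow-up, but ends all data collection once consent to the trial is withdrawn.

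**The concern.** A Poisson model with its default variance takes the variance of each participant's count to equal its mean. Two features of this design make that doubtful. Each participant has several infusion episodes followed by monthly adverse-event enquiry, so a susceptible participant may contribute many events. And the count is defined over a fixed 12 months although some participants will be observed for less. Without an offset, differences in observation time enter the count as extra variance. If losses differ between arms, they also bias the rate ratio.

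At stake is how far the interval for the adverse-event rate ratio can be trusted. An interval that is too narrow makes chance differences in tolerability look firmer than they are.

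**Working it through.** **The plan's own figures.** The article gives no rate, dispersion, alpha or power for the adverse-event comparison, so there is no such figure to reproduce. The sample size, from which the dropout allowance is taken, does reproduce:
- Hazard ratio: ln(0.8)/ln(0.5) = 0.322.
- Schoenfeld events, one-sided 5%, 80% power: 4 × (1.645 + 0.842)² / (ln 0.322)² ≈ 19.25, or 20 rounded up.
- Divided by the mean event probability (0.2 + 0.5)/2 = 0.35: 55.0 to 57.1 participants, against the stated 56.
- Dropout: 12/40 = 30%, and 56/0.70 = 80.

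**Effect of overdispersion.** Let φ be the ratio of variance to mean of the per-participant count. The default standard error is too small by a factor √φ, so a nominal two-sided 5% test has true error 2 × [1 − Φ(1.96/√φ)].

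| φ (assumed) | SE too small by factor | True error |
|---|---|---|
| 1 | 1.00 | 5% |
| 1.5 | 1.22 | 11% |
| 2 | 1.41 | 17% |
| 3 | 1.73 | 26% |
| 5 | 2.24 | 38% |

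Simulation of null trials with gamma-Poisson counts (40,000 per setting) agrees to within about one percentage point, for 28 or 40 per arm and for mean counts of 2, 5 or 10.

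**Effect of the remedy.** In the same simulations, with the Poisson mean model kept, a Pearson-scaled standard error gave 4.7% to 5.2% and a robust one 5.2% to 7.3%. The robust figure was highest with 28 per arm, mean count 2 and φ = 5. The negative binomial model was not simulated.

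**Effect of unequal follow-up alone.** Suppose every participant has the same rate λ per year, 30% drop out at times uniform over the year, and no offset is used.
- Mean exposure: 0.7 × 1 + 0.3 × 0.5 = 0.85 years.
- Variance of exposure: (0.7 × 1 + 0.3 × 1/3) − 0.85² = 0.80 − 0.7225 = 0.0775.
- φ = 1 + λ × 0.0775/0.85. For λ = 3, 6 and 10 this is 1.27, 1.55 and 1.91.
- True error by the formula above: 8.2%, 11.5% and 15.6%. Simulation gives about 8%, 11% and 16%. With log follow-up time as offset it returns to 5%.

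That calculation lets each participant drop out independently, so the number lost varies by chance between arms. If exactly 12 were lost in each arm, total exposure per arm would have mean 28 + 12 × 0.5 = 34 and variance 12 × 1/12 = 1. The effective ratio is then 1 + λ/34 = 1.09, 1.18 and 1.29, and the true error 6.0%, 7.1% and 8.5%. The dropout fraction is the plan's; the rates and the timing of dropout are assumptions.

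**The case against.** The strongest reply is that the article does not fix what is criticised. It names model families in one sentence and hands the detail to an analysis plan that is not shown. Overdispersion and offsets are ordinary content for such a plan, and a robust or scaled variance with an offset is still a Poisson model. This stands as mitigation: the announced plan may already contain the safeguard, and the article's silence does not show that an offset is excluded. It does not remove the point, because a model has been chosen for a named outcome and, taken with its defaults, it is not the best choice.

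A reader might infer that this model will produce false safety differences. The documents do not support that. They give no adverse-event rate and no dispersion; at φ = 1 the test is correct, and even at φ = 5 some 62% of null trials would show no false difference. They also state no decision rule for adverse events. The one-sided 5% level belongs to the primary outcome ("time-to-remission hazard ratio of 0.322 with a one-sided type I error rate of 5% and a power of 80"%), and the adverse-event totals "over the 12-month follow-up period will be presented by randomised group". The logistic analysis of serious adverse events works at participant level, so clustering of events within a participant does not affect it, though it covers serious events only.

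Nor should the 30% be read as expected lost time. The article calls it a cautious allowance, and participants who only stop treatment remain under observation.

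**Conclusion.** The point holds as a conditional one. It requires that the model be fitted with its default variance and no offset, and that counts be overdispersed or follow-up unequal. The tabulated error of 11% to 26% rests on assumed values of φ from 1.5 to 3. Unequal follow-up on the planned dropout allowance would by itself give roughly 6% to 16%, depending on the assumed event rate and on whether losses are balanced between arms. There is no contradiction in the document and no certain error in the results. This is an inexpensive improvement to a secondary safety comparison, with no bearing on the primary analysis or the sample size.

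**What to change.** In Statistical analysis methods, or in the announced analysis plan, replace the bare reference to Poisson models with one sentence: adverse-event counts will be compared with a negative binomial model, or a Poisson model with a robust or quasi-likelihood variance, with the log of each participant's observed time within the 12-month window as offset. If the analysis plan already says this, nothing more is needed.

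The cost is one sentence and somewhat wider intervals. If the Poisson mean model is kept, the scaled variance held its level slightly better than the robust one at these sample sizes. Follow-up time can be derived from visit and withdrawal dates, so no further data collection should be required.

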### Trial management

The ethical and safety aspects of the trial (e.g. rate of severe adverse events/severe adverse reactions) will be reviewed by the Data Monitoring Committee.

The DMC will meet (virtually if necessary) at least annually to consider the safety data emerging from the trial. The committee may request unblinded data and more frequent listings if necessary. The DMC reports to the CI and the Trial Steering Committee.

The TSC will provide overall supervision with respect to the conduct of the trial. Full details of the TSC and DMC membership and remit can be found in the TSC and DMC Charters. Both are available from the CI on request.

The Trial Management Group (TMG) (CI, Principal Investigators (PIs), trial statistician, trial coordinator, psychiatrists and project manager) meets weekly, manages the trial overall and discusses key decisions.

### Data protection and patient confidentiality

All investigators and trial site staff involved in this trial will comply with the requirements of the Data Protection Act 1998 and Trust Policy with regards to the collection, storage, processing and disclosure of personal information and will uphold the Act’s core principles.

Only anonymised data will be received by the trial coordination team. Patient personal data will be kept locally at each site in secure locked cabinets or electronically on encrypted secure drives.

### Insurance

Cambridge University Hospitals NHS Foundation Trust, as a member of the NHS Clinical Negligence Scheme for Trusts, will accept full financial liability for harm caused to participants in the clinical trial through the negligence of its employees and honorary contract holders. There are no specific arrangements for compensation should a participant be harmed through participation in the trial if no-one has acted negligently.

The University of Cambridge will arrange insurance for negligent harm caused as a result of protocol design and for non-negligent harm arising through participation in the clinical trial.

### Monitoring, audit and inspection

All trial documentation and related records will be available should a Medicines and Healthcare products Regulatory Agency (MHRA) Inspection or a monitoring visit or audit of the Sponsor’s representative occur. The Sponsor’s monitoring frequency will be determined by an initial risk assessment performed prior to the start of the trial. A detailed monitoring plan will be generated detailing the frequency and scope of the monitoring for the trial. Throughout the course of the trial, the risk assessment will be reviewed and the monitoring frequency adjusted as necessary. Remote monitoring will be conducted for all participating sites. The scope and frequency of the monitoring will be determined by the risk assessment and detailed in the Monitoring Plan for the trial.

### Publications policy

Ownership of the data arising from this trial resides with the trial team. On completion of the trial, the data will be analysed and tabulated and a Final Trial Report prepared. The funders of the trial will be acknowledged. Participants will be informed of the outcome of the trial through the trial website. The trial findings will be reported in peer-reviewed journals.

## Discussion

The SINAPPS2 trial has significant potential implication for the understanding and management of psychosis. Consequently, it could have a profound impact on the improved health of a group of patients presenting with psychosis.

Anti-inflammatory treatments have been shown to have some beneficial effects in schizophrenia. Although immunotherapy is already used to treat psychosis patients with neurological disease, this is the first randomised controlled trial designed to test immunotherapy for patients with anti-neuronal membrane antibodies and acute psychosis without co-occurring severe neurological disease. The SINAPPS2 trial will contribute to a limited but growing body of evidence about the role of pathogenic anti-neuronal membrane antibodies in psychosis.

The data from open non-randomised studies [16, 17] using IVIG and PLEX for patients with acute psychosis and presence of anti-neuronal membrane antibodies are promising. Findings suggest that IVIG and PLEX have a positive safety profile, and IVIG but not PLEX is acceptable to participants. Psychosis symptoms of participants in both studies were improved. The SINAPPS2 trial will investigate patients’ views on acceptability and safety of combined IVIG with rituximab. The clinical pathway for these patients is still not clear and may be a challenge during the trial, but the SINAPPS2 trial has the potential to explore and introduce an efficient clinical pathway for assessment and treatment of patients with antibody-associated psychosis in neurology clinics.

## Limitations

The study will provide evidence on the efficacy of treatment but its effectiveness would still have to be tested in a future phase of the trial. All participants will continue with their antipsychotic medication treatment during the trial. This may mask the detection of the actual effect of immunotherapy or distinguishing effects of each treatment (antipsychotics and immunotherapy). The design of the trial, specifically the method of the IMP administration, has introduced potential selection bias. The trial participants are required to endure intravenous treatments over several hours per day. This may be difficult for patients with extremely severe psychosis symptoms and they may not be initially included in the trial. However, they may be re-approached when the severity of their symptoms no longer prevents them undertaking lengthy intravenous treatment.

## Trial status

Valid trial protocol at time of submission: v3; 20/12/2018.

Participants are currently being recruited and enrolled. The recruitment began on 25 September 2017 and the first participant was enrolled on 27 September 2017. At the time of submission there were seven enrolled participants. The estimated end date of the recruitment is 31 December 2020 and the trial completion date is 31 December 2021. The populated SPIRIT [22, 23] checklist is provided as Additional file 1.

Contact: www.sinapps.org.uk; [contact]; @SINAPPS_group; @SINAPPSgroup.

## Abbreviations

AE: Adverse event
CCTU: Cambridge Clinical Trials Unit
CI: Chief Investigator
CRF: Case Report Form
CSF: Cerebrospinal fluid
CTIMP: Clinical Trial of Investigational Medicinal Products
DMC: Data Monitoring Committee
FBC: Full blood count
GABA-A: Gamma-aminobutyric acid subunit A
GCP: Good Clinical Practice
HIV: Human immunodeficiency virus
IMP: Investigational Medicinal Product
IVIG: Intravenous immunoglobulin
LFT: Liver function tests
LGI1: Leucine-rich glioma inactivated 1 antigen
MHRA: Medicines and Healthcare products Regulatory Agency
NMDAR: N-methyl-D-aspartate receptor
PANSS: Positive and Negative Syndrome Scale
PeLR: Personal Legal Representative
PLEX: Plasma exchange
PrLR: Professional Legal Representative
REC: Research Ethics Committee
SAE: Serious adverse event
TMG: Trial Management Group
TSC: Trial Steering Committee
VGKC: Voltage-gated potassium channel complex
